### Secondary Outcomes

The secondary outcomes are as follows:

Proportion of newborns stimulated or with airways cleared using a suction bulb, catheter or a bag and mask to resuscitate per 1000 facility live births.Proportion of children breastfed within an hour of birth per 1000 facility live births.Proportion of newborns that were given breast milk and no other food or drink for the first 7 days of life, per 1000 facility live births.Proportion of newborns dried and wrapped immediately after birth, per 1000 facility live births.Proportion of newborns immediately placed on the chest of the mother—skin to skin after birth per 1000 facility live births.Proportion of newborns who were not bathed within the first 24 hours of life, per 1000 facility live births.Proportion of all newborns who received all four elements of ENC: immediate and thorough drying, immediate skin-to-skin contact, delayed cord clamping, and initiation of breastfeeding in the first hour.Proportion of neonatal hypothermia, per 1000 facility live births.Proportion of newborns referred from CSCOM to a higher-level facility because of obstructed labor, low birth weight, hypothermia, or severe infection.Proportion of newborn mothers who experienced postpartum hemorrhage in the facilities.Proportion of deliveries referred to the higher-level facility from a primary facility because of postpartum hemorrhage, per 1000 deliveries.

### Sample Size

A sample size of 600 births per cluster was calculated to have 80% power to detect a reduction in the perinatal mortality rate from 30% to 27% live births, which corresponds to a 10% reduction in the perinatal mortality rate between intervention and control arms (α=5%, intracluster correlation of 0.003, and coefficient of variation of cluster size 0.9 and a 0.96 correlation of baseline measures with outcome). The number of clusters available per arm was 28. The expected average number of deliveries per month in each cluster was approximately 38, resulting in 16 months of follow-up. Two additional months of data collection are planned to account for losses and refusals and allow for adjustments in the analysis, resulting in a final average cluster size of approximately 675 births over 18 months.

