### Primary Outcome

The perinatal mortality rate per 1000 live births occurring in each facility and the corresponding catchment area for the births that had taken place in the facility will be used to assess the effectiveness of the intervention. It is defined as the sum of *fetal deaths* (stillbirth), defined as the death of a fetus weighing 500 g or more, or of 22 weeks of gestation or more, occurring in health facilities, and *early neonatal death*, namely, the death of a live born within the first 7 days of life occurring in the facility or in the community. As health facility studies are not an appropriate source of data for calculating perinatal mortality incidence [24] unless all babies are born and stayed in a health facility for 7 days, the data on perinatal mortality will be extracted from both facility-level data and household survey questionnaires.

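### The stated 80% power for a 10% reduction rests on a 0.96 baseline correlation that the plan's own ICC and cluster size cannot support; power is about 12% for the analysis described

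*Protocol article*

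**What the plan says.** All the power inputs stand in the Sample Size section of the protocol article:

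- Claim: "A sample size of 600 births per cluster was calculated to have 80% power".
- Effect: a "reduction in the perinatal mortality rate from 30% to 27% live births". The section equates this with a relative fall of one tenth.
- Error rate and clustering: "α=5%, intracluster correlation of 0.003".
- Size variation and baseline: "coefficient of variation of cluster size 0.9 and a 0.96 correlation of baseline measures with outcome".
- Clusters: "The number of clusters available per arm was 28".

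Three other places bear on the point. The Primary Outcome section expresses the outcome as "The perinatal mortality rate per 1000 live births occurring in each facility". The Results section describes the analysis as a cluster-level comparison by a chi-square statistic adjusted for clustering, and names no baseline covariate. The abstract expects about 600 deliveries per cluster but a total of 30,000 newborns in 84 facilities.

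**The concern.** Two things look wrong, and they differ in weight.

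The percent signs conflict with an outcome measured per 1000. This is a slip of units. It costs no power, but it must be resolved before the calculation can be checked.

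The serious matter is the 0.96. A facility's observed mortality rate carries binomial noise, and at 600 births with about 30 deaths per 1000 that noise is large relative to the between-facility variance implied by an ICC of 0.003. Two noisy measurements of the same facility cannot be expected to correlate at 0.96. The credit taken for that correlation turns an underpowered design into one that appears to have 80% power.

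At stake is how the primary result is read. The 80% figure tells readers that a 10% reduction would probably be detected. If the true figure is a fraction of that, a non-significant result says little about a 10% effect.

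**Working it through.** **Inputs** (Sample Size section): k = 28 clusters per arm, m = 600, ICC ρ = 0.003, CV of cluster size 0.9, r = 0.96, α = 5%. Sidedness is not stated; I assume two-sided. The article gives no formula. I use the usual one for unequal clusters, with a factor 1 − r² for baseline correlation, because it returns the stated power.

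**1. Reproducing the stated 80%**

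- Design effect: 1 + ((0.9² + 1) × 600 − 1) × 0.003 = 1 + 1085 × 0.003 = 4.255.
- Baseline factor: 1 − 0.96² = 0.0784. Net design effect: 4.255 × 0.0784 = 0.334.
- Births per arm without clustering, 30 vs 27 per 1000: (1.96 + 0.842)² × (0.03 × 0.97 + 0.027 × 0.973) / 0.003² ≈ 48,300.
- Births needed: 48,300 × 0.334 ≈ 16,100. Available: 28 × 600 = 16,800.
- Power: 81.6% (normal), 80.2% (t, 54 df). The plan's figure is reproduced.

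Read literally as 30% vs 27% with r = 0.96, the same inputs give about 100% power, and about 11 births per cluster would suffice. So the rates were entered per 1000.

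**2. What the net design effect implies**

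A value of 0.334 credits the cluster trial with three times the information of an individually randomised trial of the same size. Adjusting for a cluster-level baseline can remove between-cluster variance. It cannot remove the binomial variance within clusters.

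**3. The correlation the inputs allow**

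- Reliability of an observed cluster rate: R = mρ / (1 + (m − 1)ρ) = 1.8 / 2.797 = 0.644.
- Same-size baseline, true facility rates perfectly stable: expected r = R ≈ 0.64.
- Error-free baseline: expected r = √R ≈ 0.80.
- If 0.96 is instead the stability of true facility rates: usable r = 0.96 × 0.644 ≈ 0.62.
- An expected r of 0.96 with a same-size baseline would need m = 0.96 × 0.997 / (0.003 × 0.04) ≈ 7,976 births per cluster, or at m = 600 an ICC of 0.96 / (0.96 + 600 × 0.04) ≈ 0.038.

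**4. Power for 30 vs 27 per 1000**

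Effective n per arm = 16,800 / (4.255 × (1 − r²)); power = Φ(0.003/SE − 1.96), with SE = √(0.05537/n). For r = 0, n = 3,948, SE = 0.00375 and power = Φ(−1.16) ≈ 12%.

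| Assumption | Net design effect | Power | Reduction detectable at 80% power |
|---|---|---|---|
| No baseline adjustment (as described) | 4.255 | 12% | 33% (30 to about 20 per 1000) |
| r = 0.62 | 2.63 | 17% | 26% |
| r = 0.64, same-size baseline | 2.49 | 18% | 26% |
| r = 0.80, error-free baseline | 1.52 | 27% | 20% |
| No clustering at all | 1 | 38% | 17% |

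A simulation (beta-binomial clusters, CV 0.9, weighted cluster-level analysis of covariance, 2,000 runs) gave 19% power with a same-size baseline and 36% with an error-free one. Efficient weighting can therefore do somewhat better than the r = 0.80 row, but the no-clustering row remains the ceiling.

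**5. Fewer births**

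The abstract's total implies 30,000 / 84 ≈ 357 births per cluster. The design effect is then 2.94 and R = 0.52. Power is about 11% unadjusted and 14% with a same-size baseline.

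**The case against.** **0.96 may mean something else.** A reader might infer that the value is simply impossible. The article does not support so flat a statement, because its wording does not say which correlation is meant. As the stability of true facility rates over time, 0.96 is a possible value. But on that reading the usable correlation is about 0.62, power is about 17%, and the stated 80% is not reproduced. The 1 − r² factor is likewise inferred from the match to 80%.

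**The percentages may be literal.** With 30% vs 27% and no baseline credit, power is 84%. That reading discards the stated 0.96 and means 300 deaths per 1000 under an outcome defined per 1000. Equally, a reader might infer that the percent sign undermines the power. It does not: it is a unit slip.

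**A fuller analysis plan may adjust for baseline.** It may, and its absence from an article is no finding. But power for the analysis as printed is the unadjusted figure. The adjusted figures hold only if such an analysis is used and a baseline mortality measure exists; the only baseline that the article describes is a December 2016 facility assessment. Even an error-free baseline leaves power below 40% at 600 births per cluster.

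**Large clusters might permit a higher correlation.** Entering a size-weighted mean cluster size in the reliability formula raises the cap, but that holds only under size-squared weighting, which the article does not describe. Without weighting, size variation lowers the expected correlation.

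**The trial is complete.** This stands as a reason to disclose a correction beside the historical calculation and not overwrite it. The article also nowhere says that a null result would be read as absence of effect.

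**Conclusion.** The point holds in this form: the 80% power for a 10% reduction is not delivered by the inputs printed beside it. It appears only when 0.96 is used as an observed facility-level correlation, and that value is out of reach at ICC 0.003 and 600 births per cluster. Power is about 12% for the cluster-adjusted chi-square described in the Results section. With baseline adjustment it is about 18% with a same-size baseline and 27% at r = 0.80.

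The conclusion does not hang on the design-effect formula. With no clustering whatever, power is 38% at 600 births per cluster and 42% at the inflated size of 675; a one-sided 5% test at 600 reaches only 50%. It does rest on reading the rates per 1000, which is the reading that both the outcome definition and the reproduced 80% support. At 357 births per cluster, power is lower still.

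**What to change.** - Give the rates as 30 and 27 per 1000 births.
- Add a disclosed correction, beside the original calculation, that an observed baseline-outcome correlation of 0.96 is not attainable with ICC 0.003 and 600 births per cluster. Say which correlation was meant.
- Restate power for a 10% reduction as about 12% for the cluster-adjusted chi-square, with a detectable reduction at 80% power of about 33% (30 to about 20 per 1000).
- If a baseline-adjusted analysis is used, identify the baseline and state about 18% with one of the same size (detectable reduction about 26%), and at most about 27% at r = 0.80 (about 20%). Note that power stays below about 40% under any weighting.
- State that these figures assume 600 births per cluster, and that at the roughly 357 implied by the abstract's total they fall to about 11% (unadjusted) to 14% (same-size baseline).

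The cost is wording only, with no extra births or data. The downside is that the stated power becomes much less favourable.

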### Data Collection Methods

#### Health Facility Data

All the facilities in the intervention and control clusters will be visited once a month to retrospectively and systematically collect detailed data from partographs and registries for all facility births and any newborn that was not delivered in the facility but was referred to the facility for PNC within the first 7 days following birth.

#### Household-Level Interviews

The data collectors will also conduct a follow-up home visit (during the monthly health facility data collection visit, described above) to all women who recently gave birth in facilities since their last visit to administer a short questionnaire after at least 7 days postpartum to capture any perinatal death, complications, or adverse events, the status of the newborn during the perinatal period, and the mother’s satisfaction with the health care during the facility delivery.

#### Verbal Autopsy in the Household

In the case of perinatal death in the household recorded during their monthly visits, the data collector will pay a visit after the 40-day bereavement period to conduct a verbal autopsy. Two local independent physicians will review each completed verbal autopsy and assign the cause of death using International Classification of Diseases 10th Revision. If the two physicians do not assign the same diagnosis, a third physician (adjudicator) will review the two causes of death and assign a final cause of death.

#### Process Data From Audits and Training

The intervention trainers will collect data on the implementation of audits and training, the training modules provided, and the data on the health providers’ skills, using a structured checklist to examine providers’ skills related to AMTSL, ENC, and PNC. To ensure the quality of the data and training, supervisors will work full-time to monitor the data collection and training process and to check the reliability and accuracy of data compared with facility registries. Given the length of the project and action of multiple nongovernmental organizations in the study area, we will prospectively collect data on the concurrent implementation of MNCH interventions and health care worker training in the study facilities that may affect the study outcomes.

All data will be collected on tablets using ODK Collect and then uploaded to the server in real time. We will use a monitoring tool to oversee, in real time, the process of intervention implementation for evaluation. The study monitoring data included the number of health providers in the health facility trained, the number of community health workers trained, and the number of on-site case-based focused LDHF sessions conducted.

### Data Management and Analysis

#### Blinding

Owing to the nature of the intervention, facility staff cannot be blinded to the study allocation. Independent data collectors not involved in the intervention delivery will collect data to minimize bias in data collection. The primary outcome data analysis will be blinded to the intervention status of the facilities.

#### Data Safety Monitoring

To assess the progress and help ensure the validity and credibility of the trial results, a data and safety monitoring board will be convened with 3 individuals, respectively an epidemiologist from the Hospital for Sick Children, an obstetrician gynecologist, and a pediatrician from the University of Science and Technology of Bamako. Interim analyses will be conducted during the course of the trial, based on accumulating data on efficacy, to help the data and safety monitoring board determine whether there is sufficient evidence to recommend whether to continue, emend, or terminate the trial or if there is already clear evidence that (1) the intervention is beneficial, (2) the intervention is either harmful or has little or no effect, or (3) the trial will likely be unable to detect the effect of the intervention, for example, because the incidence of perinatal mortality and morbidity is too low or because of the low follow-up rate of the mothers during the perinatal period.

#### Process Evaluation

As this study is a complex intervention delivered in the context of an operational research, we will undertake a mixed methods process analysis to provide policy makers and practitioners information about how and why the intervention was effective and how it might be replicated [25,26]. First, the process evaluation will explore whether the intervention is delivered as intended [27], both at the facility level (training) and the individual level (provider delivery). Second, process evaluation will allow exploring the mechanisms through which interventions affect perinatal mortality and morbidity. As the intervention may have different effects in different facilities even if implementation was identical [28], we will assess the variability in the implementation to provide an understanding of how contextual and factors related to health facility features could act synergistically to influence the intervention implementation and perinatal mortality and to identify the contextual factors most likely to lead to successful implementation in other settings.

The process evaluation will be conducted in both intervention arms using the study monitoring data, semistructured interviews with stakeholders (n=12) and focus groups with facility providers and community health workers. Health care providers will be asked about their experiences and satisfaction with the intervention and suggestions to improve care for the AMTSL, ENC, and PNC. Health care providers will be asked about their perception of how to strengthen and sustain this intervention and other efforts to improve care for the AMTSL, ENC, and PNC in Mali. These steps will also help identify barriers to and facilitators of intervention implementation. Details on the protocol of our mixed methods process evaluation will be published in a separate paper.

#### Economic Evaluation

We will undertake an economic evaluation to determine the incremental cost-effectiveness of each of the case-based focused LDHF hands-on training strategies in comparison to MNCH refresher training in a classroom setting. This assessment will be conducted from the perspective of the health system. The resources used to deliver the intervention, including staff, training, implementation, and monitoring costs, will be used to derive the costs. The efficacy measurement will be based on the primary outcome variable of this study, namely perinatal mortality with a one-year time horizon and expressed in terms of the number of healthy years of life lost because of premature mortality [29]. The cost-effectiveness of the intervention will be measured in dollars per disability-adjusted life-year (DALY) saved, and we will estimate the incremental cost-effectiveness ratios of each training strategy compared with traditional training methodology by dividing the difference in mean costs between groups by the difference in mean effects between groups measured by DALYs. We will compare the LDHF hands-on training group with the traditional training in terms of (1) costs incurred over the 12-month period and (2) DALYs. All costs will be adjusted for inflation using the Malian Consumer Price Index and presented in international dollars.

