### Study Arms

#### Overview

This study is a three-arm cluster randomized controlled trial including one control and two intervention arms with a gradual increase in the intervention components.

MNCH refresher training and follow-up: the control arm will consist of standard MNCH refresher training delivered in the classroom using multi-method classroom training delivered as part of the larger Canadian Red Cross and Malian Red Cross project. For these training sessions, two maternal and neonatal health care providers from each facility randomized to the control study arm received 10-day classroom training on AMTSL, ENC, PNC, and integrated community case management of childhood illnesses.Audit and feedback with LDHF hands-on training and 6 months follow-up: the first intervention arm will include 28 facilities in which mortality and morbidity audits will be implemented by the study team, followed by one day of case-based focused LDHF hands-on training biweekly for 6 months.MNCH refresher training followed by audit and feedback combined with LDHF hands-on training and 6-month follow-up: the second intervention arm will include 28 facilities that will benefit from MNCH refresher training, in addition to mortality and morbidity audits implemented by the study team, followed by one day of case-based focused LDHF hands-on training biweekly for 6 months.

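### The cost-effectiveness ratios compare each LDHF arm with control only, so they cannot show whether adding the classroom course pays; the one-year horizon also needs rewording

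*Protocol article*

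**What the plan says.** The Economic Evaluation section of the protocol article fixes the comparison: "we will estimate the incremental cost-effectiveness ratios of each training strategy compared with traditional training methodology". The Abstract sets the same comparator, classroom MNCH refresher training, for each LDHF strategy. No ratio of one intervention arm against the other is planned.

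The Overview under Study Arms describes "one control and two intervention arms with a gradual increase in the intervention components". The control arm receives the 10-day classroom course. Arm 1 receives audits with LDHF training and no course. Arm 2 receives the course and audits with LDHF training.

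On the effect, the section takes the trial's main endpoint as its basis and describes it as "perinatal mortality with a one-year time horizon and expressed in terms of the number of healthy years of life lost because of premature mortality". Further on, it sets the groups against each other in terms of "costs incurred over the 12-month period and (2) DALYs".

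**The concern.** A health ministry can adopt only one of the three strategies for a given facility. If audit plus LDHF works, the next question is whether to keep the classroom course alongside it. That is arm 2 against arm 1. Two ratios that share the control arm as reference do not answer it. A costlier arm can show an acceptable average ratio against control while its last increment of cost buys little or nothing.

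The second difficulty is wording. Years of life lost to a stillbirth or first-week death extend over a lifetime, so a one-year horizon on that measure makes sense only if it governs the period in which deaths and costs are counted. The section does not say so. Cost-effectiveness is named in the Abstract's objective and is a secondary objective in the text, so both matters affect a reported result, though not the primary outcome.

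**Working it through.** **1. What each contrast measures.** Let M be the cost of the classroom course and A the cost of audit plus LDHF, and assume the two add. From the Study Arms section, control costs M, arm 1 costs A, and arm 2 costs M + A.

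| Contrast | Incremental cost | Planned? |
|---|---|---|
| Arm 1 vs control | A − M | yes |
| Arm 2 vs control | A | yes |
| Arm 2 vs arm 1 | M | no |

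Neither planned ratio isolates what the course adds to audit plus LDHF.

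**2. How far the ratios can diverge.** The section gives no costs, DALYs or ratios, so there is no plan figure to reproduce. The inputs for an illustration are:

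- Births per arm over 12 months: 28 facilities × 38 deliveries per month × 12 = 12,768 (Sample Size section).
- Deaths averted in arm 1: 12,768 × 0.003 = 38.3, taken as 38. This reads the planned 10% reduction as 30 to 27 per 1000; the section prints these as percentages.
- Life-years per death: 27.8 (assumed 60 years at 3%; formula in step 3).
- Costs, assumed: A = 180,000 and M = 80,000, so arm 1 costs 100,000 more than control and arm 2 costs 180,000 more.

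Arm 1 vs control: 100,000 / (38 × 27.8) = 95 per DALY. For arm 2, under three assumed effects:

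| Deaths averted, arm 2 vs control | Arm 2 vs control | Arm 2 vs arm 1 |
|---|---|---|
| 46 | 180,000 / (46 × 27.8) = 141 | 80,000 / (8 × 27.8) = 360 |
| 40 | 180,000 / (40 × 27.8) = 162 | 80,000 / (2 × 27.8) = 1,439 |
| 38 | 180,000 / (38 × 27.8) = 170 | no gain at higher cost: dominated |

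The ratio against control moves only from 141 to 170, while the ratio that decides between the arms goes from 360 to dominance.

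**3. The horizon.** Life-years lost per death are L undiscounted, or (1 − exp(−rL)) / r at rate r. L and r are assumptions; the document gives neither.

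| L (years) | Undiscounted | r = 3% |
|---|---|---|
| 50 | 50 | 25.9 |
| 60 | 60 | 27.8 |
| 70 | 70 | 29.3 |

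If the one-year horizon were applied to life-years, each death would count about 1. Cost per DALY would then be inflated by the table's values: about 26 to 29 times at 3%, or 50 to 70 times undiscounted. This factor is common to all arms. It leaves their ranking unchanged but shifts every ratio against any cost-per-DALY threshold.

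**The case against.** The plan answers the question it sets, each LDHF strategy against current training, and computes nothing wrongly. The arm 2 versus arm 1 increment follows by subtracting the two increments against control. That is true of the point estimate, and it is why the fix is cheap. It does not follow from the ratios alone, and a reader given two ratios against control has no prompt to do the subtraction. The costs in the illustration are invented; they show that the problem can arise, not that it will.

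An article condenses a fuller plan, and methods for uncertainty or net benefit may properly sit there. This point does not rest on their absence. The comparator and the horizon are written down here.

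Stronger readings are tempting, and the document does not support them:

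- **That life-years are capped at one.** The section never says that years per death are truncated. Counting deaths over one year and valuing each over a lifetime is a natural reading.
- **That costs and effects cover different windows.** A reader might set "costs incurred over the 12-month period" against the 14 months of data in the Abstract or the 16 and 18 months in the Sample Size section. But the same section gives the effect one year too. The costs are those of delivery: "The resources used to deliver the intervention, including staff, training, implementation, and monitoring costs, will be used to derive the costs". Audit and LDHF training run for 6 months, so 12 months could capture all of it.
- **That arm 1 saves money against control.** Its incremental cost is net of the course it omits, but no costs are given, so the sign is unknown.

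**Conclusion.** The comparator point holds. Ratios against control alone cannot show whether the classroom course is worth adding to audit plus LDHF, and they may mislead by making a dominated or poor-value arm 2 look acceptable. The size depends on costs and effects that the document does not give; under the assumed inputs the gap is 162 against about 1,440 per DALY.

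The horizon point holds as unclear wording. The 26- to 29-fold (3%) or 50- to 70-fold (undiscounted) inflation applies only if the horizon is taken literally for life-years, with an assumed life expectancy of 50 to 70 years. It cannot be said that the evaluation will mislead, only that it may unless both matters are settled.

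**What to change.** Replace the control-only ratios with a fully incremental analysis. Rank the three strategies by cost, remove any that are dominated, and report each ratio against the next best remaining strategy, with arm 2 versus arm 1 included. It uses the costs and deaths already planned for each arm. The downside is one extra contrast, estimated less precisely because the difference between two active arms is likely to be small.

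Reword the horizon: one year is the period over which costs and deaths are counted, and each death is valued over remaining life expectancy. This costs one sentence. The article says that data cleaning or analysis was only beginning at submission, so both changes were still feasible then.
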